#### Primary and Secondary Outcomes

The primary and secondary outcomes and potential mediators are listed in Table 2. Our primary outcome is COVID-19 vaccination intention, which will be an important outcome during the 1-week follow-up period. The baseline, posttest (3-day), and follow-up (1-week) surveys will assess the participants’ vaccination intention. A 5-point Likert scale questionnaire will measure the intention to be vaccinated against COVID-19. The participants will be asked, “If a vaccine for Coronavirus (COVID-19) becomes available, would you want to receive it?” and provided the response options “1=Definitely Would Not Want It, 2=Would Likely Not Want It, 3=Neutral or Unsure, 4=Would Likely Want It, and 5=Definitely Would Want It.” The level of vaccine acceptance is defined as willing (“Definitely Would Not Want It,” and “Definitely Would Want It”) or hesitant (“Definitely Would Not Want It,” “Would Likely Not Want It,” and “Neutral or Unsure”). The secondary outcomes include knowledge level related to COVID-19, which will be assessed using a validated questionnaire that has been used in numerous studies [34,35], and decisional conflict, which will be assessed using the decisional conflict scale [36]. In addition, psychological stress owing to decision-making regarding COVID-19 vaccination will be measured.

**Table 2 table2:** Study outcome measures.

			Baseline measurement (day 1)		Posttest measurement (day 3)		Follow-up measurement (day 7)
**Primary outcome**							
	COVID-19 vaccination intention	✓		✓		✓	
**Secondary outcomes**							
	Knowledge about COVID-19 vaccination	✓		✓		✓	
	Decisional conflict	✓		✓		✓	
	Stress related to COVID-19 vaccination	✓		✓		✓	
	Perceived benefits of COVID-19 vaccination	✓		✓		✓	
	Perceived barriers to COVID-19 vaccination	✓		✓		✓	

### Data Collection and Management

We collected quantitative data on the potential mediators of implementation effects, including attitudes toward COVID-19 vaccination (eg, perceived benefits and barriers). Questionnaires which were validated for web-based use and apply Checklist for Reporting Results of Internet E-Surveys items were designed to measure primary and secondary outcomes. Data collection is performed according to standard guidelines. To improve the reliability of data quality, real-time support through instant messages or phone calls regarding data collection were provided during the entire data collection period. The respondents entered a web-based data collection program, self-assessed through web-based questionnaires, which the research team reviews and rechecks for anomalous responses according to a defined monitoring strategy. If an error was found in the data, the research team asked the rater to correct or explain it, and all corrections were made after the research team confirms them. In addition, to facilitate retention, respondents reported any issues with the respondent. In the event of study discontinuation, a report was generated in a concise format. All available data were checked by the research team members. Every respondent was assigned a unique study ID, and the research team trained the researchers to protect the study data to ensure data safety. The data collection form does not contain any personally identifiable information. The password-protected electronic files were stored on a password-protected computer. Data managers and analysts independently conducted inspections for each evaluation.

### Sample Size and Power

We sought to detect the main effects of the communication intervention within the 3 groups with at least 90% power using a 2-sided α of .05. We used G*Power (latest version 3.1.9.7; Heinrich-Heine-Universität Düsseldorf) to calculate the sample size for 3 repeated measurements (in-between interaction, small effect size of 0.2). Our target analytic sample size was 450 (150 per study group) participants. To achieve this analytic sample size, we randomized a projected 630 participants (210 per study group) and expected approximately 30% of the initial participants to drop out during the 7-day follow-up period.

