## Methods

### Study Design

A randomized controlled trial (RCT) will be conducted and reported according to the CONSORT-EHEALTH (Consolidated Standards of Reporting Trials of Electronic and Mobile Health Applications and Online Telehealth) checklist, and the protocol timeline is shown in Table 1. This study is a 3-arm prospective RCT enrolling >450 participants with underlying medical conditions (Figure 1). The participants who complete their baseline web-based questionnaire will be recruited into the study and randomly assigned to 3 equal groups, stratified by their underlying disease, sex, age, and willingness to receive a COVID-19 vaccine (willingness and hesitation). The participants will be randomized to receive (1) standard information about COVID-19 vaccination (control group), (2) COVID-19 vaccination DA (intervention group *SMART-DA*), or (3) COVID-19 vaccination DA with targeted information provision (intervention group *SMART-DA*-α). Each group is described in detail in the following sections. After 1 week, we will follow-up with the participants and use an intention-to-treat (ITT) approach to determine the effects of their COVID-19 communication intervention on COVID-19 vaccination. There is no expected harms or unintended effects in each group.

**Table 1 table1:** Spirit figure protocol timeline.

			Enrollment		Pretreatment assessment		Allocation		Postallocation assessment				Close out
Time point			-t_1_		0		0		t_1_		t_2_		t_3_

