### Study Procedures and Implementation Strategies

#### Randomization

A representative sample of 450 individuals will be randomly selected through a proportional stratified sampling method based on sex and age from a list of candidates registered with the research company. The D-optimal blocking procedure proposed in a recent study [30] will be used for random assignment to reduce interference on the intervention effect by covariates such as the individual’s underlying disease, sex, age, and intention to receive COVID-19 vaccination. D-optimality is based on the determinant of the information matrix for the design, which is the same as the reciprocal of the determinant of the variance-covariance matrix for the least squares estimates of the linear parameters of the model. The D-optimal blocking procedure uses a SAS/QC procedure OPTEX (version 9.4; SAS Institute) to randomly allocate the participants to 1 of the 3 arms by all the researchers. The assigned participants will be blinded so that they do not know whether they belong to the intervention group or control group. Both the assigned participants and data analysts will be blinded, and the data analysts will conduct effect analysis of the anonymized groups 1, 2, and 3 without being aware of whether the group is an experimental or control group. However, because the researcher providing the intervention is aware of which group the participants belong to, the study is single blind.

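### The planned 450 does not follow from the stated sample-size inputs, and 90% power, a small effect of 0.2 and 450 agree only under an unstated high correlation

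*Protocol article*

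**What the plan says.** Under Sample Size and Power, the protocol article states its aim as follows: "We sought to detect the main effects of the communication intervention within the 3 groups with at least 90% power", at a 2-sided alpha of .05. It names the software ("We used G*Power (latest version 3.1.9.7; Heinrich-Heine-Universität Düsseldorf") and says this was used to "calculate the sample size for 3 repeated measurements (in-between interaction, small effect size of 0.2". The result is an analytic target of 450, or 150 per arm. For attrition it adds: "we randomized a projected 630 participants (210 per study group) and expected approximately 30% of the initial participants to drop out".

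The section does not say whether 0.2 is Cohen's f or a standardised mean difference d. It gives no correlation between repeated measurements, no sphericity correction and no SD.

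Other sections give other numbers. Randomization says: "A representative sample of 450 individuals will be randomly selected". The abstract and Study Design give more than 450. Table 4 shows 172 + 172 + 171 = 515 allocated, and Table 3 shows 446 with all three responses. (The Results text prints 466 for the latter, but 515 − 69 = 446.)

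**The concern.** The section states enough of a calculation to be checked: software, test, number of measurements, effect size, alpha and power, with three equal arms from Study Design. Three things look wrong.

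- The answer is several times larger than that test returns for f = 0.2.
- The stated target is main effects, but the test sized is the group-by-time interaction. These are different hypotheses with different sample sizes.
- The label small fits 0.2 as a standardised mean difference. It does not fit 0.2 as f for this interaction.

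At stake is how the result will be read. Someone who accepts 90% power for a small effect of 0.2 could take a null finding on vaccination intention as evidence against a small benefit. Whether the design supports that depends on a metric and a correlation that the section does not give.

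**Working it through.** **Inputs.** From the article: k = 3 arms, m = 3 measurements, alpha .05, power .90, effect 0.2, target N = 450. Assumed, because not stated: correlation ρ from 0 to .8 and sphericity factor ε from 1 to 0.5 (the lower bound for m = 3).

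**1. Attempt to reproduce 450 with f = 0.2.** G*Power's within-between interaction uses a noncentral F with λ = f²·N·m·ε/(1−ρ), df1 = (k−1)(m−1)ε and df2 = (N−k)(m−1)ε. At ρ = .5, ε = 1 and N = 67, λ = 0.04 × 67 × 3/0.5 = 16.08 on 4 and 128 df, and power is 90.2%. At N = 66 it is 89.7%. The required N over the range is:

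| ρ | ε = 1 | ε = 0.5 |
|---|---|---|
| 0 | 131 | 214 |
| .3 | 93 | 151 |
| .5 | 67 | 109 |
| .7 | 41 | 67 |
| .8 | 29 | 46 |

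Other f = 0.2 variants at the same alpha and power, rounded up to equal groups:

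- Cohen-style effect-size option: 195 (321 at ε = 0.5).
- SPSS-style option: 198 (324 at ε = 0.5).
- Between-groups main effect: 111 to 279 for ρ from 0 to .8.
- One-way ANOVA: 321.

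None is close to 450. Figures near 450 appear only when a stated input is replaced. For example, f = 0.1 gives 516, 362 and 260 at ρ = 0, .3 and .5, so 450 would need ρ of about .13 (516 × 0.87 ≈ 449).

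**2. Power of 450 at f = 0.2.** At ρ = 0 and ε = 1, λ = 0.04 × 450 × 3 = 54 on 4 and 894 df, and power exceeds 99.9%. At ρ = 0 and ε = 0.5 it is 99.8%. Higher ρ only raises it.

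**3. How large f = 0.2 is here.** Take a step of d SD in both decision-aid arms at both post-baseline visits, with arm-by-visit means (0,0,0), (0,d,d), (0,d,d). After removing arm and visit effects, the nine interaction terms are 4d/9 once, −2d/9 four times and d/9 four times. The root mean square is √[(16 + 16 + 4)/(81 × 9)]·d = 2d/9. So f = 0.2 corresponds to d = 0.9, and d = 0.2 corresponds to f = 0.044.

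**4. Power if 0.2 means a 0.2 SD arm difference, with 150 per arm.**

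- Pairwise, unadjusted: noncentrality 0.2/√(2/150) = 1.73, power 41%.
- Day 7 adjusted for baseline: divide by √(1−r²). Noncentrality is 2.00 at r = .5 (51%) and 2.43 at r = .7 (68%). Power is 82% at r = .8 and 91% at r = .85.
- Omnibus interaction: λ = 450 × 3 × 0.0444²/(1−ρ) = 2.667/(1−ρ). This gives 3.81, 5.33 and 8.89 at ρ = .3, .5 and .7, with power 30%, 42% and 65%. Power is 85% at ρ = .8 and 90% at ρ = .83.
- Mean of both post visits adjusted for baseline: residual variance (1+ρ)/2 − ρ². Power is 68%, 82% and 92% at ρ = .5, .7 and .8.

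**5. Difference detectable with 90% power at the size obtained.** This uses a day-7 pairwise test with 446/3 ≈ 149 per arm (equal split assumed; Table 3 does not give arms). It is 0.38 SD unadjusted, 0.33 SD at r = .5 and 0.27 SD at r = .7. With all 515 it would be 0.35, 0.30 and 0.25 SD.

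**6. Attrition.** 630 × 0.7 = 441 and 450/0.7 = 643. Going from 630 to 450 is a loss of 1 − 450/630 = 28.6%.

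**The case against.** The strongest reply is that nothing here shows an underpowered trial. The article never defines 0.2 as a difference in SD units, and at the literal G*Power input of f = 0.2 a sample of 450 has over 99% power. The claim of at least 90% is then true. A reader might combine the two readings and infer that power is far below 90%, or that the trial had even odds or worse of finding a small benefit. The document does not support that flat statement, because it needs d in place of f and a modest correlation as well. The outcome is the same item asked at days 1, 3 and 7, so a high correlation cannot be excluded, and mixed models over repeated measurements are planned. This part of the reply stands.

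The reply does not rescue the section. On the f reading, 450 was not derived from 0.2 and the effect is not small. On the d reading, 90% power depends on a correlation that is not given. A condensed article may leave ρ to a fuller document, but no ρ from 0 to .8 turns the stated inputs into 450.

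Two smaller defences largely succeed. A loss of 28.6% is fairly called about 30%, so the attrition step is a rounding matter. More than 450 is compatible with both 630 (labelled a projection) and 515 (the number obtained). Only the 450 under Randomization, which matches the analytic target and not the number to be randomised, needs reconciling with 630.

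**Conclusion.** The point holds in this form: the stated sample size is not reproducible from the stated inputs. The named interaction at f = 0.2 needs 67 at ρ = .5 and ε = 1, and 29 to 214 over ρ 0 to .8 and ε 1 to 0.5. The largest standard f = 0.2 variant tried gives about 324, against 450 stated. The section also targets main effects while sizing an interaction, and it calls small an f that equals a step of about 0.9 SD in both decision-aid arms.

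The three statements of 90% power, a small effect of 0.2 and 450 do not hold together unless 0.2 is read as an SD difference and a high correlation is assumed: about .83 to .85 for the interaction or the baseline-adjusted day-7 test, or about .8 for the adjusted mean of both post visits. At lower correlations, power for a sustained 0.2 SD difference is 30% to 65% for the interaction (ρ .3 to .7), and 41% unadjusted to 68% adjusted (r = .7) for the pairwise test. These figures assume equal arms, common variance and correlation, and the same step at both post visits. They do not establish that the trial was underpowered for an effect the protocol itself defined.

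**What to change.** Restate Sample Size and Power. Nothing is recruited, re-randomised or re-analysed.

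1. Name the hypothesis that was powered (main effect, interaction or a specific contrast), the effect metric (f or d) and the assumed correlation and sphericity correction, so that the figure can be reproduced. If the inputs behind 450 can no longer be recovered, say so.
2. Replace the claim of 90% power for a small effect of 0.2 with the difference detectable with 90% power at the size obtained, with the correlation shown. For a day-7 pairwise comparison at 446 completers this is about 0.38 SD unadjusted, 0.33 SD at r = .5 and 0.27 SD at r = .7. The authors may choose another contrast, provided it is named. Label this as a description of the sample obtained and not as the original planning calculation.
3. Reconcile the planned numbers: 450 under Randomization, 630 under Sample Size and Power, and 515 allocated in Table 4.
4. Minor: give the attrition as 28.6%, or note that exactly 30% would need 643.

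The cost is a few sentences. The stated power will probably look less favourable than the present text.

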### Statistical Methods

#### Evaluation of Efficacy

We will also examine the descriptive statistics for the participants’ baseline characteristics and compare them across the 3 study groups. The main analysis will be performed based on the ITT principle, involving all the randomized participants to investigate the effectiveness of the interventions. The ITT principle can minimize potential bias owing to dropouts and can be applied while performing further preprotocol analyses. The effects of the interventions on the primary outcome (eg, vaccination intention) and secondary outcomes (ie, knowledge related to COVID-19 vaccines, decisional conflict, psychological stress related to vaccination, perceived benefits of COVID-19 vaccines, and perceived barriers to COVID-19 vaccines) will be estimated using linear mixed-effects models for continuous outcome variables and generalized linear mixed-effects models for categorical outcome variables. The test statistic will be calculated to assess any significant intervention benefit; we will use 2-sided *P* values with α=.05 to calculate the level of significance.

#### Subanalyses

We will perform a path analysis to examine the theoretical constructs as potential mediators following the effect evaluation. For each outcome, a path analysis will be performed to describe the direct and indirect relationships, including the perceived benefits of and barriers to the COVID-19 vaccine. Path models are statistical methods that, compared with multiple regressions, allow for the simultaneous assessment of several regression paths occurring between multiple dependent and independent variables and for the computation of direct, indirect (mediated), and total effects. Standardized parameter estimates (standardized β) will be used to compare the magnitude of associations between media use and mediators. The model parameters and SE estimates are to be calculated. The participants with missing data will be excluded from analysis. Statistical analyses will be conducted using STATA (version 15; StataCorp LLC), SAS (version 9.4; SAS Institute), and R (version 4.2; R Foundation for Statistical Computing) software.

In addition, we will conduct subgroup analyses according to the preintervention intent for vaccination. We will observe how the degree of vaccination intention changes in the 2 groups. Among those who have already been willing to receive a COVID-19 vaccine, there are cases in which their decisions are passive or involuntary owing to social pressure or economic activity. Therefore, we seek to identify whether the nature of their decisions changes through the intervention.

The Data Monitoring Committee comprises the Principal Investigator, independent external data managers, and statisticians. The committee is responsible for data quality throughout the data collection, analysis, and reporting processes. The Data Monitoring Committee is independent of the research funding agency and has no competing interests.

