### Measures

#### Participant’s Characteristics

Sociodemographic factors include sex (1=male and 2=female), age, family size (ie, living alone or with 1 or more person), the presence of children at home who attend school (more than one=1 and none=0), marital status (ie, married, single, divorced, or bereaved), and residence (urban=1 and rural=2). We will also assess educational level (1=middle school or below, 2=high school graduate, and 3=college and above) and monthly household income in KRW (1=<KRW 200 million, 2=KRW 200 million to 399 million, 3=KRW 400 million to 599 million, and 4=KRW ≥600 million).

Health-related factors include the respondent’s seasonal influenza vaccination history, underlying diseases, and prior COVID-19 diagnosis. For seasonal influenza vaccination history, the participants will be asked, “Have you been vaccinated against the seasonal influenza flu in the last five years?” The responses include “every year,” “more than once,” “maybe once,” “never,” and “don’t know.” We will also investigate the presence of underlying diseases by asking the participants to indicate all diagnosed underlying diseases (eg, hypertension, dyslipidemia, diabetes, chronic cardiac disease, asthma, and cancer). The participants who have not been diagnosed with underlying diseases are excluded from further study.

To examine health literacy related to COVID-19, we adapt the HLS-COVID-Q22 that has been translated into Korean. The HLS-COVID-Q22 was developed in Germany in 2020 by Okan et al [33] based on the European Health Literacy Survey Questionnaire. Its validity and reliability were verified among the German population aged ≥16 years (α=.94; *ρ*=0.891) [33]. The HLS-COVID-Q22 contains 22 items organized into 4 subgroups: accessing (6 items), understanding (6 items), appraising (5 items), and applying (5 items) health-related information in terms of COVID-19. It is answered on a 4-point scale, ranging from “4=very easy” to “1=very difficult.”

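### The path analysis relates the mediators to media use, which the article lists as neither randomised nor measured, so as worded it does not estimate mediation of the intervention effect

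*Protocol article*

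**What the plan says.** Three parts of the protocol article bear on this point.

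- **Aim.** Subanalyses opens with: "We will perform a path analysis to examine the theoretical constructs as potential mediators following the effect evaluation". Data Collection and Management describes the data as covering "potential mediators of implementation effects, including attitudes toward COVID-19 vaccination (eg, perceived benefits and barriers". The Discussion (Principal Findings) promises that the results will account for the efficacy of the intervention and what mediates it.
- **Model.** Subanalyses continues: "For each outcome, a path analysis will be performed to describe the direct and indirect relationships, including the perceived benefits of and barriers to" (the sentence ends by naming the vaccine). It says that path models yield direct, mediated and total effects. It then states that standardised coefficients "will be used to compare the magnitude of associations between media use and mediators".
- **Outcome role of the mediators.** Evaluation of Efficacy lists, for the mixed models, "secondary outcomes (ie, knowledge related to COVID-19 vaccines, decisional conflict, psychological stress related to vaccination, perceived benefits of COVID-19 vaccines, and perceived barriers". Table 2 likewise places benefits and barriers under secondary outcomes. The text introducing Table 2 says it also lists potential mediators, but the table has no such heading.

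The randomised factor is given in Study Design: "The participants will be randomized to receive (1) standard information about COVID-19 vaccination (control group"), followed by SMART-DA and SMART-DA-α.

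**The concern.** A mediation analysis in a randomised trial traces the path from allocated arm to mediator to outcome. Randomisation protects the first step, from arm to mediator, and that step is what links the analysis to the intervention. Here the only named counterpart of the mediators is media use, and the paragraph never names the arm as exposure. An analyst who followed the sentence would estimate how an unrandomised trait, with no listed measure, relates to perceived benefits and barriers. The article could then not deliver its promised account of how the decision aids work.

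A smaller gap lies in the set of outcomes. A path model for every outcome, with benefits and barriers in the paths, does not say what happens when the outcome is itself perceived benefits or perceived barriers.

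**Working it through.** The article gives no figure for this analysis, so the check is mainly a comparison of its sections.

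**1. Is media use randomised or listed as measured?**

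| Place in the article | What it lists | Media use? |
|---|---|---|
| Study Design | three arms: standard information, SMART-DA, SMART-DA-α | no |
| Table 1, assessments | sociodemographic and health-related factors, health literacy, intention, knowledge, decisional conflict, stress, benefits, barriers | no |
| Participant's Characteristics ("Sociodemographic factors include sex (1=male and 2=female), age, family size" and so on) | also children at home, marital status, residence, education, income, influenza vaccination history, underlying diseases, prior COVID-19 diagnosis, COVID-19 health literacy | no |
| Primary and Secondary Outcomes, Table 2 | intention and five secondary outcomes | no |
| Subanalyses | standardised coefficients for the mediators | yes, the only mention |

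**2. Does a media-use path carry information about the arms?** Purely as an illustration, assume these effects, none of which comes from the article: on the mediator, SMART-DA 0.3, SMART-DA-α 0.5 and media use 0.3, with media use independent of arm; mediator on outcome 0.4; direct effect of each active arm on outcome 0.1. An indirect effect is the product of its two steps.

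- SMART-DA: 0.3 × 0.4 = 0.12
- SMART-DA-α: 0.5 × 0.4 = 0.20
- Media use: 0.3 × 0.4 = 0.12

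In 2,000 simulated trials of 450 participants in three arms, a model with arm as exposure returned 0.119 and 0.200. A model with media use as predictor returned 0.123. The third product contains neither arm's effect on the mediator, so it would still be 0.12 if both arm effects were zero.

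**3. Which outcomes can sensibly be end points of a path model?** One primary and five secondary outcomes make six. Removing the two that serve as mediators leaves 6 − 2 = 4: intention, knowledge, decisional conflict and stress.

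**4. Does the order of surveys matter?** The article does not say which survey supplies mediator or outcome. A second illustration, again with assumed inputs only, shows why the choice is worth making. Mediator and outcome have unit variance and share a stable trait with loading 0.7. Same-day errors correlate 0.25, the arm raises the mediator by 0.3 SD, and the mediator has no true effect on the outcome. The trait contributes 0.7² = 0.49 and error variance is 1 − 0.49 = 0.51.

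- Same survey, no baseline adjustment: 0.3 × (0.49 + 0.51 × 0.25) = 0.3 × 0.6175 = 0.185.
- Day-3 mediator, day-7 outcome, both baselines adjusted. Let b be the coefficient of the day-3 mediator and c that of each baseline value. With same-day error present at baseline too, b + 0.98c = 0.49 and 0.49b + 1.6175c = 0.49. Hence c = 0.220, b = 0.275, and the spurious indirect effect is 0.3 × 0.275 = 0.082.
- The same model with same-day error switched off at baseline: b = 0.49 / (1 + 2 × 0.49) = 0.247, giving 0.074.

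Ordering cuts the spurious effect by more than half here, but 0.082 / 0.185 = 44% of it remains. These figures concern survey order, not the media-use error.

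**The case against.** The strongest reply is that media use is a stray term. The paragraph never formally defines an exposure, the surrounding text makes the mediation aim clear, and a condensed article need not list every questionnaire item. Part of this stands: the article shows only that media use is not listed as measured, and a slip is as plausible as a deliberate choice. But the sentence still contradicts the aim and needs correcting either way. Reading media use as use of the web tool does not rescue it. Participants could use the tools as often as they wished, so usage would be self-selected, and no usage measure is listed.

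A reader might infer three stronger criticisms that the article does not support.

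- **That the trial cannot show how the intervention works.** It can. Arms are randomised, and mediators and outcomes are surveyed at baseline, day 3 and day 7, so an appropriate model can be specified once arm is the exposure.
- **That benefits and barriers may not be both secondary outcomes and mediators.** They may. A mediator has to respond to treatment, and testing that response is an ordinary step. Only the unrestricted set of path-model outcomes needs tightening.
- **That the plan prescribes same-survey mediation.** It does not. It is silent on survey order, which an analysis plan commonly settles.

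**Conclusion.** The point holds in limited form. The stated path analysis names a predictor that is not randomised and not listed as measured, which conflicts with the article's own aim of explaining what mediates the intervention. As worded, it does not estimate mediation of the intervention effect. The open-ended outcome set is a lesser fault in the same paragraph.

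No numerical size can be attached from the article. The illustrative values above rest wholly on assumed inputs and should not be cited as the size of the error. The reach is one subanalysis; the mixed-model comparison of vaccination intention is untouched. The conclusion assumes that the fuller protocol or questionnaire does not define media use. Even if it does, the exposure for intervention mediation would still have to be the arm.

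**What to change.** 1. In Subanalyses, replace media use with two indicators for randomised arm: SMART-DA versus control and SMART-DA-α versus control. If media use was in fact collected and is wanted as a covariate, list its measure and say so separately.
2. Limit the path models to intention, knowledge, decisional conflict and stress as end outcomes. Perceived benefits and barriers stay as secondary outcomes in the mixed models.
3. Preferably, use day-3 benefits and barriers as mediators and day-7 values as outcomes, adjusting for the baseline values of both. Label the mediator-to-outcome path as non-randomised, because ordering and adjustment reduce confounding but do not remove it.

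The cost is a change of wording. It needs no new data, since every variable in the corrected model is already in the three surveys. The article says it was first submitted before data analysis. The correction should be dated and recorded before the path models are run, or reported as a later change if they have been.
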